## Abstract

**Background:**

Acute abdomen is a common disease in the emergency department (ED) and usually results in huge medical expenditure. To relieve abdominal pain effectively and reduce bed occupancy rate in emergency rooms, electroacupuncture is a practical method in the treatment of abdominal pain.

**Methods/design:**

Five hundred patients will be randomly and evenly divided into experimental and control groups. Both groups should have their basic information taken and their bilateral acupuncture points ( Hegu (LI 4), Neiguan (PC6), Zusanli (ST 36), Shangjuxu (ST37), Xiajuxu (ST39), Taichong (LR3), and Taibai (SP3)) will be intervened by electroacupuncture or vaccaria Seeds, in this clinical study. Electroacupuncture has been introduced to this experiment as an auxiliary technique. The experimental group will receive real electroacupuncture, but the control group will receive a placebo electroacupuncture in which transcutaneous electrical nerve stimulation will not be turned on. After the intervention, we will evaluate the difference in abdominal pain, the length of stay at the emergent observation ward, and the proportion of revisits with abdominal pain.

**Discussion:**

In Taiwan, medical expenditure is increasing annually because of the higher bed occupancy caused by acute abdominal pain in the hospital. We expect that the combined treatment of electroacupuncture and modern medical treatment will not only reduce bed occupancy and the length of ED stay but also effectively decrease the rate of readmission and revisits by 72 h. By means of electroacupuncture, the spiraling cost of health care can eventually be reduced.

**Trial registration:**

ClinicalTrials.gov identifier: NCT03199495. Registered on 27 June 2017.

## Background

Acute abdominal pain is one of the common symptoms in the emergency department (ED). In the USA, about 5 million patients have suffered from abdominal pain and visited the ED. These accounted for around 5–10% of all emergency patients [1, 2]. In 2014, Murata *et al*. demonstrated that ileus is the main factor leading to abdominal pain [3]. Around 8% of female and 9.1% of male patients had acute abdomen pain due to ileus. For patients over 60 years old, ileus is the major factor resulting in abdominal pain regardless of gender [3]. Therefore, finding out how to reduce acute abdominal pain effectively is an important task in EDs.

The definition of ileus is that partial or complete intestine is obstructed. Hence, the intraluminal contents cannot be excreted [4, 5]. Symptoms associated with ileus include (1) abdominal pain, (2) vomiting, (3) abdominal distension, and (4) constipation [6, 7]. Eighteen to forty-two percent of emergency patients need hospitalization [8]. Even though the patients do not meet admission criteria in spite of the persistent pain, basic medical cares in the emergency observation rooms are required. As a result, high levels of bed occupancy have been increasing. The longer patients stay in the emergency observation room, the more medical resources are wasted. Thus, hospital beds in emergency rooms cannot be used efficiently [9–12]. Furthermore, unscheduled return visits are the popular chief complaints; 19.9% of the patients with abdominal pain stayed in the ED over 6 h and then returned to the ED for a further stay [13, 14]. In 2010, Yeh *et al*. found that the cost of medical care for the returning ED visits is higher than for the initial ED visits and that the cost of medical care for other hospital ED visits are higher than for the original ED visit [15].

Compared with Western medicine, traditional Chinese medicine is considered a complementary medicine. Acupuncture is a safe therapy with low risk of adverse side effects in clinical practice [16]. It has been widely applied to treat gastrointestinal disease for many years. In 1996, the World Health Organization reported that 64 symptoms of gastrointestinal disease, such as epigastric pain, paralysis ileus, indigestion, and constipation, could be treated by acupuncture [17].

Electroacupuncture therapy is an auxiliary technique for acupuncture. Stimulating acupuncture points with pulse current through an electroacupuncture apparatus can increase gastric emptying and reduce the period of ileus after abdominal or laparoscopic surgery. Furthermore, side effects after the operation were reduced. For example, functional constipation could be alleviated efficiently [18, 19].

To the best of our knowledge, electroacupuncture has not been applied to the treatment of acute abdominal pain in EDs. In this study, we will collaborate with an ED in order to investigate whether electroacupuncture can alleviate acute abdominal pain effectively and reduce the length of stay in the emergency observation area. We expect that the combination of traditional Chinese medicine and Western medication can provide efficient treatment for patients and save medical resources.

## Methods/design

### Trial design

This is a prospective randomized controlled clinical trial with a two-arm, parallel-group design (Fig. 1). Data analysis will be performed in accordance with the per-protocol analysis.

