### Participant eligibility

We expect to recruit 500 patients and allocate them randomly to an experiment group or a control group. Patients who come to the Changhua Christian Hospital ED with acute abdominal pain will be evaluated by the attending physicians. The patients are in urgent conditions such as unstable vital signs and must stay in the hospital for further examination will be excluded by ED physicians. The consultation sheet will be issued after seeking the patients’ agreement.

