#### Sample size and randomization

The sample size calculation was based on the results of our previous pilot study by using the statistical software G*Power 3.1.9.2. The minimum sample size for estimating the difference in the mean change of visual analog scale (VAS) at 15 min between the experimental and control groups with an effect size of 0.275 (means of 1.1 and 0.6, standard deviations of 2.4 and 0.9, *n* = 26 and 28, respectively) was calculated. With these parameters, a sample size of 208 subjects in each group was needed to have 80% power and 5% level of significance by independent *t* test. With a predicted attrition rate of 10%, the minimum number of subjects required at baseline was calculated to be 229 per group. Patients meet the inclusion criteria will be randomly assigned by computer in a 1:1 ratio, and the results of this random assignment will be sequentially numbered into each sealed opaque envelope containing a card labelled ‘electroacupuncture’ (experimental group) or ‘placebo electroacupuncture’ (control group). Whenever a patient participates in the study, a sealed opaque envelope will be opened by a doctor.

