### Data management

Each group of patients will be randomly assigned by computer in a 1:1 ratio. The medical information will be documented and stored separately from personally identifiable data. Independent personnel will record data on the paper version of a case report form and input the data to the computer database. The medical information and the group allocation will not be visible to third parties. All data will be stored in the database and inspected by a person who is not involved in this study. The doctors and statistician will not have access to these data until patient evaluations are completed. If subjects withdraw from the study, no further data will be collected from them. Data already obtained will be used only in analysis of this study. Once we complete the study, we will delete the data from the database.

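### Per-protocol is the only stated analysis set in a randomised comparison seeking benefit over sham, which leaves the effect estimate open to selection bias of unknown size and direction

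*Protocol article*

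**What the plan says.** The Trial design section describes the study as follows: "This is a prospective randomized controlled clinical trial with a two-arm, parallel-group design". It then fixes the analysis principle: "Data analysis will be performed in accordance with the per-protocol analysis". That sentence is unqualified and so covers the primary outcome and both secondary outcomes. No section names an intention-to-treat, modified intention-to-treat or full analysis set. The article does not say which departures take a patient out of the per-protocol set. The Statistics section lists t tests, chi-squared or Fisher tests and a GEE model without naming a population.

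The Background gives the aim, which is to "investigate whether electroacupuncture can alleviate acute abdominal pain effectively and reduce the length of stay in the emergency observation area". No non-inferiority margin appears anywhere.

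Two further statements bear on who is analysed:

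- Sample size and randomization: "With a predicted attrition rate of 10%, the minimum number of subjects required at baseline was calculated to be 229 per group".
- Data management: "If subjects withdraw from the study, no further data will be collected from them". The next sentence there lets data already obtained be used in this study's analysis. It does not say that withdrawn or non-adherent patients are analysed as randomised.

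**The concern.** In a trial meant to show benefit, the comparison is protected only while patients stay in the groups to which they were randomised. A per-protocol set is formed after allocation, by events that may depend on the arm and on how the patient is doing.

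Three features of this design make that more than a formality:

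- **Perceptible arms.** The experimental group has needles inserted, De Qi elicited and current applied. The control group has seeds under patches with the power off. Reasons for not completing the session or the follow-up can differ between the two.
- **Known allocation.** A doctor opens the envelope when the patient joins, so the arm is known before treatment. The per-protocol criteria are not fixed in the article.
- **Subjective outcome.** The primary outcome is self-reported pain on the VAS and BPI, including an assessment at 3 days. A patient's pain can influence whether that patient remains evaluable.

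At stake are the validity of the pain comparison and of the comparisons of ED stay and 72-hour revisits, which the same sentence governs.

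**Working it through.** **Inputs from the protocol article.** Planned recruitment is 500, allocated 1:1, so 250 per group. The pilot values are given "with an effect size of 0.275 (means of 1.1 and 0.6, standard deviations of 2.4 and 0.9", a planned difference of 1.1 − 0.6 = 0.5 VAS points. Predicted attrition is 10%.

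**The plan's own figure.** The text states that "a sample size of 208 subjects in each group was needed to have 80% power and 5% level of significance by independent" *t* test. With d = 0.275:

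n = 2 × (1.960 + 0.842)² / 0.275² ≈ 208 per group (208.5 with the exact t distribution).

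The figure reproduces as a two-sided 5% test; a one-sided test would give 164. The effect size follows from SD = √((2.4² + 0.9²)/2) = 1.812 and 0.5/1.812 = 0.276. The sample size is not in dispute.

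**Size of a possible bias.** The documents do not give the share excluded or how those patients fare, so both are assumptions. All cases assume no true effect, and the pilot SDs are applied to the patients analysed.

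*Case A: exclusions from the electroacupuncture arm only.* Of 250 per arm, a fraction f of the electroacupuncture arm is excluded, and their mean change lies k points below that arm's overall mean. The retained mean then shifts by

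bias = f × k / (1 − f).

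With f = 0.10, 225 are left against 250, and SE = √(2.4²/225 + 0.9²/250) = 0.170. The rejection rate is P(|Z + bias/SE| > 1.96).

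| f | k (points) | Bias (points) | Share of 0.5 | Two-sided type I error |
|---|---|---|---|---|
| 5% | 0.5 | 0.03 | 5% | 5.3% |
| 5% | 1 | 0.05 | 11% | 6.2% |
| 5% | 2 | 0.11 | 21% | 9.7% |
| 10% | 0.5 | 0.06 | 11% | 6.2% |
| 10% | 1 | 0.11 | 22% | 10% |
| 10% | 2 | 0.22 | 44% | 26% |

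(For f = 5%, SE = 0.166.)

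*Case B: equal exclusions from both arms.* Each arm loses 10%, leaving 225 per arm, and those lost are one own-arm SD worse than those retained. Net bias = 0.10 × 2.4 − 0.10 × 0.9 = 0.24 − 0.09 = 0.15. SE = √((2.4² + 0.9²)/225) = 0.171. Then bias/SE = 0.88 and the type I error is about 14%.

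*Case C: exclusions balanced and unrelated to outcome.* The bias is zero and the type I error stays at 5%.

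**What an as-randomised analysis would cost in power.** With 250 per group and d = 0.275, power is about 87%. Suppose a share of the active arm gains nothing and so dilutes the effect. At 5%, d = 0.275 × 0.95 = 0.261 and power is about 83%. At 10%, d = 0.275 × 0.90 = 0.2475 and power is about 79%.

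**The case against.** The strongest reply is that the intervention is a single supervised 15-minute session and the sample size rests on the 15-minute VAS, so few patients may fall outside a per-protocol set for that comparison. The predicted 10% is attrition, not a per-protocol exclusion rate. Part of it may be missed 3-day contact, which an intention-to-treat label does not recover. The article names no arm-specific ground for exclusion, and data obtained before withdrawal may be used. All of this stands. It limits how large the problem can be said to be, but it does not supply an as-randomised analysis. Nor is this a detail left to a fuller document, because the article makes an affirmative choice.

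A reader might infer more than the documents support:

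- **That the bias favours electroacupuncture.** The exclusions are undefined, so the direction is unknown. Control patients who notice the inactive patches and leave because pain persists would push the estimate the other way.
- **That the false-positive rate is about 29%.** This follows if 10% of the electroacupuncture arm alone is lost, one SD (2.4) worse than those retained, with 225 per arm: 0.24/0.171 = 1.40. But it places all the informative loss in one arm while taking both arms down to 225, and the plan's 10% applies to each group.
- **That ED stay and revisits could be recovered from hospital records.** The article does not say so. It describes telephone follow-up and tracking by a research assistant.
- **That data collection after withdrawal should be extended.** Recruitment was completed by April 16, 2018 and follow-up lasts 3 days, so this can no longer be done.

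**Conclusion.** The concern holds as a fault in a stated rule. Per-protocol is the sole analysis set in a randomised comparison that seeks benefit over sham, and the set is undefined. The estimate is open to selection bias, though the documents do not show that bias will occur, how large it would be or which arm it would favour.

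The illustrations run from no inflation (exclusions balanced and unrelated to outcome), through about 14% (equal 10% loss, one own-arm SD worse), to about 26% (10% lost from one arm, 2 points below its mean). They rest on assumed exclusion rates and deficits and on the pilot SDs. Even the moderate one-arm case, 10% lost at a 1-point deficit, doubles the nominal 5%. The planned 250 per group leaves power near or above 80% for an as-randomised analysis under the dilution considered, so sample size gives no reason to prefer per-protocol.

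**What to change.** Replace the sentence in Trial design with wording such as:

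*The primary analysis will include all randomised patients in the group to which they were assigned, using all VAS and BPI data obtained, including data obtained before withdrawal. Missing VAS-2 and VAS-3 values will be handled by [stated method], with a sensitivity analysis to its assumptions. A per-protocol analysis, with criteria defined before the groups are compared, will be a sensitivity analysis.*

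The missing-data method has to be named, because an analysis of all randomised patients cannot be carried out without one when some VAS values are absent. Name the same population in Statistics, so that it also covers ED stay and 72-hour revisits.

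The cost is one sentence in Trial design and one in Statistics, with no extra patients. The downside is some dilution if non-adherent patients gain no benefit: power of about 87% falls to about 79% if 10% of the active arm gains nothing. Since recruitment is closed, the change affects analysis and reporting only. It requires that every randomised patient is still in the database, so it must be made before the deletion that Data management schedules for the end of the study. If the per-protocol analysis has already been run, report the as-randomised analysis beside it, with the exclusions and reasons by arm.

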**Fig. 1 Fig1:**
[figure not shown]
Flow chart of the study. *Abbreviations*: *BPI* brief pain inventory, *VAS* visual analog scale

### Participant eligibility

We expect to recruit 500 patients and allocate them randomly to an experiment group or a control group. Patients who come to the Changhua Christian Hospital ED with acute abdominal pain will be evaluated by the attending physicians. The patients are in urgent conditions such as unstable vital signs and must stay in the hospital for further examination will be excluded by ED physicians. The consultation sheet will be issued after seeking the patients’ agreement.

#### Inclusion criteria

Participants meeting all of the following criteria are included:
age of 20 to 90 years, either gender;the chief complaint consists of gastrointestinal symptoms, such as nausea, vomiting, diarrhea, bloating, and constipation;diagnosis with International Classification of Diseases 10th revision (ICD-10) code K00-K94: Diseases of the digestive system.

#### Exclusion criteria

Participants meeting one or more of the following criteria are excluded:
patients are not likely to follow the instructions of the trial or cannot communicate reliably with the investigator;cardiac diseases, such as arrhythmia, or equipped with cardiac pacemaker, deep brain stimulator, or other electronic implants;abnormal vital signs;serious injuries;physical symptoms of a neurological problem;the situation of ileus needs surgery;pregnancy status;mental disabilities or unconsciousness.

#### Participating center/physicians

This study will be conducted in the ED at Changhua Christian Hospital. All of the traditional Chinese medicine doctors in this research have more than 10 years of acupuncture experience.

#### Sample size and randomization

The sample size calculation was based on the results of our previous pilot study by using the statistical software G*Power 3.1.9.2. The minimum sample size for estimating the difference in the mean change of visual analog scale (VAS) at 15 min between the experimental and control groups with an effect size of 0.275 (means of 1.1 and 0.6, standard deviations of 2.4 and 0.9, *n* = 26 and 28, respectively) was calculated. With these parameters, a sample size of 208 subjects in each group was needed to have 80% power and 5% level of significance by independent *t* test. With a predicted attrition rate of 10%, the minimum number of subjects required at baseline was calculated to be 229 per group. Patients meet the inclusion criteria will be randomly assigned by computer in a 1:1 ratio, and the results of this random assignment will be sequentially numbered into each sealed opaque envelope containing a card labelled ‘electroacupuncture’ (experimental group) or ‘placebo electroacupuncture’ (control group). Whenever a patient participates in the study, a sealed opaque envelope will be opened by a doctor.

#### Interventions

The emergency physicians will issue the consultant sheet. After receiving the completed informed consent forms, the research assistant will interview the patients and their families, explain the plan and purpose of research, and collect basic information, including age, gender, height, weight, family medical history, history of drinking alcohol and smoking, body mass index, vital signs, blood/biochemical test, and medical imaging. The research assistant will then inform the traditional Chinese medicine physician who will give immediately medical treatment. Before treatment, the research assistant will assess the brief pain inventory (BPI) and VAS of the patients.

##### Experimental group: electroacupuncture

Patients in the experimental group will receive electroacupuncture with electrostimulation by using a Ching Ming electroacupuncture device. Disposable, sterilized acupuncture needles (length of 40 mm, diameter of 0.27 mm; Tennyson Medical Instrument Developing Co., Ltd., Taiwan) will be inserted to a depth of 15–35 mm. Needles are inserted correctly and are manually stimulated until the “De Qi” sensation is elicited. Among the seven acupunctural points mentioned above, only Hegu (LI 4), Neiguan (PC6), Zusanli (ST 36), and Taichong (LR3) with electrical stimulation are conducted. The frequency of electrical stimulation is 2 Hz, and the intensities of the stimulation are below 9.8 mA for 15 min [20]. Once it is completed, the investigators will remove the acupuncture needles and start the BPI and VAS after 15 min.

##### Control group: sham electroacupuncture

Sham electroacupuncture is delivered by Vaccaria seeds which are categorized as spherical, smooth, and hard. Patients in the sham acupuncture group receive sham electroacupuncture by using Vaccaria seeds which are secured onto the same acupuncture points as the experimental group and then covered by patches of transcutaneous electrical nerve stimulation with the power off. The control variable in this study is carried out with the electrical stimulation off. After 15 min, the investigators will remove Vaccaria seeds and patches of transcutaneous electrical nerve stimulation.

During the study, all participants will receive Western conventional therapy simultaneously, and the researchers are responsible for recording all of the data and for the safety of patients. If any hemorrhages, bruises, or swelling occur after pulling out needles, the doctor will directly make provisions for the patients. For example, putting ice packs on the bruised area can be useful for absorbing bruises. After treatment, all of the patients should be followed up by a phone interview within 3 days.

### Outcomes

#### Primary outcome

Abdominal pain is registered and evaluated by the BPI and VAS. The BPI is used to assess the severity of pain and the impact of pain on daily functions. The VAS is graded from 0 (no pain) to 10 (severe pain). Patients are evaluated at three time points in this study: before intervention (VAS-1), after intervention (VAS-2), and 3 days after the intervention (VAS-3).

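### The primary outcome combines two pain instruments and two post-treatment times without ranking them, while the power and 5% level cover only VAS change at 15 minutes

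*Protocol article*

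**What the plan says.** Protocol article, Primary outcome: "Abdominal pain is registered and evaluated by the BPI and VAS". On the BPI it adds: "The BPI is used to assess the severity of pain and the impact of pain on daily functions". On timing: "Patients are evaluated at three time points in this study: before intervention (VAS-1), after intervention (VAS-2), and 3 days after the intervention (VAS-3". Neither instrument and neither post-treatment time is put first. The Secondary outcome section lists only the length of ED stay after treatment and the 72-hour revisits, so it does not demote the BPI or 3-day pain.

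Sample size and randomization: the stated target is "estimating the difference in the mean change of visual analog scale (VAS) at 15 min between the experimental and control groups". The assumed standardized difference is 0.275, taken from pilot results (mean changes 1.1 and 0.6, SDs 2.4 and 0.9). For a t test on independent groups at 80% power and a 5% level, the section arrives at 208 per group. For losses: "With a predicted attrition rate of 10%, the minimum number of subjects required at baseline was calculated to be 229 per group". Participant eligibility plans 500 patients in total.

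The Discussion explains that the VAS was used for sizing because a BPI score is built up from questionnaire items. The Statistics section plans Student's t tests between groups, paired t tests of pre-post change in VAS and BPI, and a linear model fitted by generalized estimating equations (GEE). It names no primary contrast, time point, hierarchy or success rule, and no significance level.

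**The concern.** A power statement should describe the endpoint on which the trial will be judged. Here the outcome labelled primary has several components, and the power statement covers one of them. Nothing in the article prevents the primary claim from resting on 3-day VAS or on the BPI if VAS at 15 minutes is null. The choice could then be made after the results are known, and the error rate attached to the claim would not be the 5% used in sizing. If instead every component had to be positive, the planned power would not apply.

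**Working it through.** **1. The plan's own figure.** Inputs from Sample size and randomization: means 1.1 and 0.6, SDs 2.4 and 0.9, power 80%, level 5%.

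- Effect size: d = (1.1 - 0.6) / sqrt((2.4² + 0.9²)/2) = 0.5 / sqrt(3.285) = 0.276. The plan has 0.275.
- Per group, two-sided: n = 2(1.960 + 0.842)² / 0.275² = 207.6, so 208. The exact noncentral-t solution is 208.5, and power at 208 is 79.9%. A one-sided 5% test would need only about 165, so the calculation is two-sided.
- Attrition: 208 × 1.10 = 228.8, so 229. Dividing by 0.90 would give 232. The planned 250 per group covers either.

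The stated 208 therefore belongs to one two-sided 5% test of VAS change at 15 minutes.

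**2. How many comparisons the primary outcome contains.** The count is not fixed by the text.

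- Two: one treatment effect per instrument, for example from a GEE that pools the post-treatment times.
- Three: VAS-2, VAS-3 and BPI after treatment. The interventions section places the BPI before treatment and at the post-treatment assessment, and the time labels are for VAS only.
- Four: the same plus BPI at 3 days, inferred from the sentence that patients are evaluated at three times.

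The paired t tests are pre-post comparisons, not comparisons between groups, and are not counted.

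**3. Error rate if any one significant result counts as success.** This rule is an assumption, as is 5% per test outside the sizing calculation. For k independent tests the rate is 1 - 0.95^k. For correlated tests it comes from simulating equicorrelated normal statistics (1,000,000 draws). The correlations are assumed, since the documents give none.

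| Comparisons | Independent | ρ = 0.5 | ρ = 0.7 | ρ = 0.9 |
|---|---|---|---|---|
| 2 | 9.75% | 9.1% | 8.4% | 7.1% |
| 3 | 14.3% | 12.5% | 10.9% | 8.4% |
| 4 | 18.5% | 15.7% | 13.0% | 9.4% |

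**4. If all comparisons must be significant.** The error rate stays at or below 5%, but joint power cannot exceed that of the weakest component. As an illustration, with 80% power for each and independence, it is 0.80² = 64% for two and 0.80⁴ = 41% for four. Positive correlation raises these figures towards 80%. The article gives no effect size for BPI or 3-day VAS, so actual joint power cannot be computed.

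**5. What each remedy does to the sample size** (d = 0.275 assumed for every comparison).

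- Single primary endpoint: 208 evaluable per group, as now. Power is 86.6% with 250 evaluable per group, or 82.9% with 225 (250 less 10%).
- Four co-equal endpoints with Bonferroni, 0.05/4 = 0.0125 each: 297 evaluable per group, or 297/0.90 = 330 enrolled. Power per test is 61.6% at 208 and 71.5% at 250.

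**The case against.** The strongest reply is that the intended primary endpoint is evident. The sample size is built on VAS at 15 minutes, the Discussion again treats VAS as the reference measure for sizing, and multiplicity rules commonly sit in an analysis plan or full protocol that is not shown. The GEE may also yield one treatment effect per instrument.

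Part of this stands. Silence on adjustment is not itself a fault here. The 5% appears only with the sizing test, and for that test it is correct. The GEE could reduce the family to two comparisons. What does not stand is that the sizing settles the endpoint. The Primary outcome section puts BPI and VAS on equal terms, and the Discussion's reason for using VAS explains a calculation without demoting the BPI. With one GEE effect per instrument there would still be two tests. The mismatch lies between two statements within the article.

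A reader might infer more than the documents support:

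- **That the stated 5% is wrong, or that the error is about three times 5%.** The article claims no family-wise rate. A factor near three needs four comparisons, low to moderate correlation and an any-one-wins rule. None of these is fixed in the text.
- **That there are at least four tests.** BPI at 3 days is an inference: the follow-up is described as a phone interview, and the schedule figure is not available here. Four is closer to a ceiling than a floor.
- **That the BPI's severity and function parts add further tests.** The article describes both but plans no separate analysis of them.
- **That BPI function items cannot be interpreted minutes after treatment.** Nothing in the article establishes this, and the point does not depend on it.

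**Conclusion.** The point holds in a limited form. The primary outcome as written is not a single endpoint, and the 80% power and 5% level describe only one component of it. If one positive comparison at 5% were enough, the chance of a false-positive primary result would lie between about 7% and 18.5%, depending on the number of comparisons and on correlations that have to be assumed. If all had to be positive, the error rate would be controlled but the 80% power would not hold. Neither reading matches the stated pair of figures. The mismatch itself is certain; the size of the inflation is not. It should be corrected because it leaves the primary claim open to choice after the results are seen, and the correction is cheap.

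**What to change.** In the Primary outcome section, name one endpoint: the between-group difference in change from VAS-1 to VAS-2, stating that VAS-2 is the 15-minute assessment used for sizing, tested at two-sided 5%. Move VAS-3 and all BPI scores to the secondary outcomes, either with Holm adjustment or with a statement that they carry no confirmatory claim. In the Statistics section, say which analysis delivers the primary contrast.

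The required number stays at 208 evaluable per group and nothing further has to be collected. The cost is that BPI and 3-day pain can no longer support the primary claim. If the investigators want to keep them as primary, they need a stated hierarchy or a split of the 5% level. With an equal four-way split, the numbers exceed the 250 per group planned.

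The Trial status section reports recruitment as complete, so the change should be dated and recorded before unblinded analysis. If that analysis has already taken place, the choice should be disclosed as post hoc.
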